**Fig. 9 Fig9:**
[figure not shown]
Mandibular advancement oral appliance and thermosensitive microchip TheraMon®

The MAD concept in the dental sleep field has been used to evaluate the therapeutics effectiveness of OA_m_ therapy, which is compounded by efficacy (immediate result) plus adherence to treatment over time [39–41]. The measurement of objective compliance is important because it is necessary to know if any therapy continues to have positive results over time. With this information it is possible to determine the MDA and so the therapeutic effectiveness. The meaning of the effectiveness of any therapy is compounded by efficacy plus adherence to such treatment over time [51–53].

### Quality control

In order to ensure data quality, the dentists responsible for performing the EMG examination, as well as the sleep technicians responsible for the polysomnography examination, will receive appropriate training. External monitoring will be carried out periodically to verify the performance of EMG and polysomnography.

Guidance on the correct use and performance of each therapy will be given at each appointment, and all participants/caregivers will have access to an exclusive telephone number to solve any doubts they may have during the study, in order to avoid any misunderstanding that may compromise the results. This telephone contact will also be an instrument to reinforce the given guidelines and to encourage adherence to the therapies.

It will be explained to the participants/caregivers that they will be excluded whenever physiotherapy or speech therapy is to be undertaken during the study.

In addition, all participants/caregivers will be aware that they are free to withdraw their participation from this study at any time if they so wish, with no penalties.

If the participants face any difficulties to perform the proposed therapy, then they will be allocated to another therapy that they are able to perform.

The data obtained prior to and 2 months after all proposed therapies will be analyzed by “blind” evaluators. In addition, satisfaction, acceptance, and side effects will be assessed after a 2-month period, for each therapy applied.

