### Randomization

After evaluation of the eligibility criteria, the subjects will be randomly distributed into the three intervention groups. Randomization numbers will be generated using envelopes, which will contain a card stipulating to which group the subject will be allocated. The envelopes will be sealed and opaque in texture, in order to ensure confidentiality. Participants will be allocated, enrolled, and assigned to the study by two assistants who will not participate in the intervention stage. Participants will be contacted by telephone.

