### Sample size

Power analysis or Power test is the process used for determining the sample size for this study, using SPSS (version 22.0.0.0). This is based on a work entitled “Effects of Neuromuscular Electrical Stimulation on the Masticatory Muscles and Physiologic Sleep Variables in Adults with Cerebral Palsy: A Novel Therapeutic Approach” [15]. The intervention was considered to result in a minimum effect similar to the EMG activity of the masseter and temporalis muscles in disabled adults. Thus, the sample size obtained revealed that 90% reliability to identify a relevant outcome will be present at the bidirectional α level of 0.05 with 10 subjects deemed necessary in each group, to which five individuals will be added to compensate for possible dropouts. Due to the risk of withdrawal, 45 patients will be recruited.

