#### Phases of the surface electromyography examination

The sEMG, referring to the bilateral masseter (surface portion) and to the temporal (anterior portion) muscles in rest, MVC, MHI, and bite force, shall be carried out in two distinct phases: Phase 1, initial data acquisition, prior to proposed therapies (Groups 1–3); and phase 2, treated groups (Groups 1–3) after 2 months of neuromuscular electrical stimulation, mastication apparatus with mastication instrument Hiperboloide®, and mandibular advancement oral appliance therapies. The obtained data will be compared among each group and among each person with themselves, to verify the effectiveness of the proposed therapies on the improvement of the masticatory muscle electrical activity, on the physiological sleep variables, and on salivary parameters in patients with DS.

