### Statistical analysis

Whenever applicable, the data will be presented as average ± standard deviation. The paired *t* test will be used in order to compare continuous variables with normal distribution, prior to and after polysomnography, as well as specific therapies. If the data show a non-normal distribution, then the Wilcoxon test will be used. The groups will be compared to one another using ANOVA or Mann–Whitney U test, according to the distribution. *P* ≤ 0.05 will be considered statistically significant. Missing data will be treated as worst-case scenario imputation. All analyses will be performed using SPSS 16.0.

All data will be stored on a notebook exclusively for this purpose, as well as on a hard disk for increased safety of data storage. Data will be allocated to a file with a number that corresponds to each participant and will be managed by the assistants, not available to the professionals who will carry out the interventions.

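### Participants are re-allocated by ability and excluded for other therapy after randomisation, and nothing ties them to the arm drawn, which leaves the between-group comparison open to selection bias

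*Protocol article*

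**What the plan says.** The Randomization section of the protocol article states that "the subjects will be randomly distributed into the three intervention groups", using sealed, opaque envelopes. The Quality control section then sets two rules that operate once a participant is in the trial:

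- **Change of therapy:** if participants have any difficulty carrying out their assigned therapy, "then they will be allocated to another therapy that they are able to perform".
- **Exclusion:** participants and caregivers are told that "they will be excluded whenever physiotherapy or speech therapy is to be undertaken during the study".

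The section on phases of the electromyography examination describes the follow-up assessment as "phase 2, treated groups (Groups 1–3) after 2 months of neuromuscular electrical stimulation" and the other two therapies. The Statistical analysis section says: "The groups will be compared to one another using ANOVA or Mann–Whitney U test, according to the distribution". For missing values it says only: "Missing data will be treated as worst-case scenario imputation".

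The article does not say in which group a participant who changes therapy is counted. It does not say whether an excluded participant is still assessed at 2 months, or whether the missing-data rule covers that participant.

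**The concern.** Randomisation makes the three groups comparable at the moment the envelope is opened. Both rules alter the groups after that moment. The first is mandatory, is triggered by any difficulty, and chooses the destination by ability rather than chance. The trial has only three therapies, so the natural reading is a move into another randomised arm, and the verb is the one used for the envelope assignment. The second removes randomised people because of an event during follow-up.

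Difficulty is unlikely to be spread evenly. Electrical stimulation is given in three 20-minute sessions a week, the mastication apparatus is bitten for 5 minutes six times a day, and the oral appliance is worn only in sleep. Difficulty with biting could plausibly go with poor masticatory function, which the Abstract lists among the primary outcomes. If movers are counted where they end up, or if excluded participants disappear, a difference between groups may reflect who stayed rather than what the therapies did. With 10 to 15 people per arm, a handful of such participants can matter.

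**Working it through.** **1. The plan's own figures.** The Sample size section gives a two-sided α of 0.05, 10 per group and 5 more per group for dropouts. The total reproduces: 3 × (10 + 5) = 45. The 10 per group cannot be reproduced, because no effect size or standard deviation (SD) is stated. The allowance of 5/15 = 33% is for dropouts; switching is not mentioned.

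**2. Inputs for the illustration.** From the document: 15 recruited per arm, three arms, 5% significance level. Assumed, because the documents give nothing: no true therapy effect; outcomes standard normal; in one arm the k participants with the highest difficulty score move to one other arm; correlation ρ between difficulty and a poor outcome.

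**3. Expected bias when movers are counted by therapy received, k = 4.** The expected values of the four largest of 15 standard normal scores are 1.736, 1.248, 0.948 and 0.715, with average 1.16. So:

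- movers' mean outcome = −1.16ρ
- stayers' mean (11 people) = +(4 × 1.16ρ)/11
- receiving arm's mean (15 + 4 = 19 people) = −(4 × 1.16ρ)/19
- difference = 4 × 1.16ρ × (1/11 + 1/19) = 0.67ρ

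This gives about 0.33 SD at ρ = 0.5 and 0.53 SD at ρ = 0.8, although no therapy effect exists.

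**4. False-positive rates by simulation, 15 per arm, no true effect.**

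| Scenario | Test | ρ = 0.5 | ρ = 0.8 |
|---|---|---|---|
| 4 moved one way | pairwise t test | 12–13% | 28% |
| 4 moved one way | three-group ANOVA | 10–11% | 21% |
| 4 moved, split over both other arms | three-group ANOVA | 9–10% | 18% |
| 4 moved from each arm to the next | three-group ANOVA | about 3% | about 2% |
| 4 excluded from one arm, none moved | pairwise t test | about 8% | about 15% |
| Analysed as randomised | either | about 5% | about 5% |

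One mover at ρ of 0.3 to 0.5 gives 5% to 6% by ANOVA. With 2 to 5 one-way movers and ρ from 0.3 to 0.8, the pairwise t test ranges from 6% to 36%.

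**5. A second model.** Here a share of one arm moves to the other and strugglers have an outcome 0.5 or 1 SD worse, in whichever arm they are. With shares of 10% to 30%, the false-positive rate by therapy received is 5.5% to 12.2% at 10 per group and 5.5% to 17.4% at 15 per group.

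**6. Cost of analysing as randomised.** Switching dilutes a true difference. The standardised effect implied by 10 per group, 90% power (reading the stated 90% reliability as power) and two-sided 0.05 is (1.960 + 1.282) × √(2/10) = 1.45. If a share c of one arm switches into its comparator, the effect becomes 1.45 × (1 − c). For c = 0, 10%, 20% and 30%, power is 90%, 83%, 74% and 62% at 10 per group, and 98%, 95%, 89% and 79% at 15 per group.

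**The case against.** The strongest reply is that the change-of-therapy rule describes what a struggling participant receives, not how that participant is analysed. The Aims and hypotheses section defines Groups 1–3 by randomisation, so the groups in the Statistical analysis section could mean the groups as drawn. A condensed article may leave the analysis set to a fuller document. This stands in part. A reader might infer that the plan prescribes analysis by therapy received, but no sentence says so. What the article does fix is a second, non-random allocation and an exclusion, and both need correcting whatever a fuller plan contains.

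Three further inferences are tempting but unsupported:

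- **That the bias is irreversible.** For switching it is not: if 2-month outcomes are collected, analysing as randomised restores the 5% rate. It is permanent only for excluded participants who are not followed up.
- **That a moved participant cannot complete 2 months on the new therapy.** This assumes a clock fixed at randomisation. The article times assessment by 2 months of therapy and does not say whether the clock restarts after a move.
- **That the receiving arm must look worse.** Direction and size depend on movement being one-way and linked to prognosis. Eligibility already requires responding to commands such as biting and relaxing, which may limit switching.

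Worst-case imputation is not said to cover excluded participants. If it did, it would still be no substitute for observed outcomes.

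**Conclusion.** The concern holds as a fault in two stated rules, not as a missing intention-to-treat sentence. Followed literally, they change the composition of the randomised groups for reasons that can relate to therapy and outcome, and nothing in the article restores those groups for the comparison.

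The size is unknown. Under one-way, prognosis-linked movement of 4 in 15, the nominal 5% error rate roughly doubles (ANOVA, correlation 0.5) or rises to more than five times nominal (t test, correlation 0.8). With a single mover, or moves in all directions, there is little or no inflation. These percentages rest on assumed switching rates and correlations and should be read only as illustrations. The change should be made before the comparison is relied on, because outcomes of excluded participants that are never collected cannot be recovered later.

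**What to change.** 1. State that every participant is analysed in the arm drawn from the envelope, with the 2-month assessment timed from randomisation whatever therapy is used later.
2. Reword the change-of-therapy rule so that it records the change, its date and its reason without altering the analysis group.
3. Keep participants who start physiotherapy or speech therapy in follow-up and in the analysis set, and record that use.
4. Present any analysis by therapy received as a labelled sensitivity analysis.

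Whether a participant may change therapy is left to the trial team.

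The cost is protocol wording, a field for the therapy actually used, and follow-up of participants who would otherwise have been excluded. Switchers dilute true differences. The loss of power is small if few switch, but grows as shown in the working, for example from 98% to 89% at 15 per group if 20% of one arm switch under the implied effect.

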### Statistical analysis

Whenever applicable, the data will be presented as average ± standard deviation. The paired *t* test will be used in order to compare continuous variables with normal distribution, prior to and after polysomnography, as well as specific therapies. If the data show a non-normal distribution, then the Wilcoxon test will be used. The groups will be compared to one another using ANOVA or Mann–Whitney U test, according to the distribution. *P* ≤ 0.05 will be considered statistically significant. Missing data will be treated as worst-case scenario imputation. All analyses will be performed using SPSS 16.0.

All data will be stored on a notebook exclusively for this purpose, as well as on a hard disk for increased safety of data storage. Data will be allocated to a file with a number that corresponds to each participant and will be managed by the assistants, not available to the professionals who will carry out the interventions.

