**Methods:**

The patients with DS will be randomly selected and divided into three groups (DS-NMES, DS-MA, and DS-OA_m_) with a minimum of 10 patients in each group. A thermosensitive microchip will be embedded in the OA_m_ to record its compliance. The therapeutic effects on masticatory muscle function will be investigated through electromyography, a caliper, and a force-transducer device; the sleep variables, in turn, will be evaluated by means of polysomnography. The physicochemical and microbiological properties of the saliva will also be analyzed, including the salivary flow, viscosity, buffer capacity, cortisol levels (susceptibility to psychological and/or physical stress), and *Pseudomonas aeruginosa* levels (risk of aspiration pneumonia) in these patients. The methods determined for this study will be carried out prior to and after 2 months of the recommended therapies.

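### The analysis rule lets 10 to 15 values per arm choose the test, sends non-normal data to raw-scale rank tests, and offers a two-group test for three arms; one model and scale per outcome should be fixed in advance

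*Protocol article*

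**What the plan says.** All of the following is in the protocol article.

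- Statistical analysis, within arm: "The paired *t* test will be used in order to compare continuous variables with normal distribution". The fallback is: "If the data show a non-normal distribution, then the Wilcoxon test will be used".
- Statistical analysis, between arms: "The groups will be compared to one another using ANOVA or Mann–Whitney U test, according to the distribution".
- The same section summarises data as mean and SD and names no transformation. It does not say whether normality is judged per arm or pooled, or on values, changes or residuals.
- Abstract (Methods): three arms, "with a minimum of 10 patients in each group". Sample size: "with 10 subjects deemed necessary in each group, to which five individuals will be added to compensate for possible dropouts", which makes 45 recruited.
- Outcomes include AHI (Subjects sets an entry threshold above 5 per hour for this criterion and states no upper limit), salivary flow, morning and night cortisol, *P. aeruginosa* counts per ml, mouth opening and EMG. The section on analysis of surface EMG data normalises EMG RMS to a percentage of maximum voluntary contraction.
- The section on phases of the EMG examination says that data are compared between groups and within each person. It does not say whether the between-group comparison uses change or the 2-month value.

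**The concern.** Four features of the stated rule are open to criticism.

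1. The test is chosen after the data are seen, from arms too small for a normality verdict to be stable. For one outcome, one arm could be judged on mean change and another on ranks, so the results would not be comparable across a row of the results table.
2. The condition is attached to the variables ("in order to compare continuous variables with normal distribution"), whereas a paired t test needs approximately normal within-person differences. Skewed values can give well-behaved differences, and the reverse.
3. The stated answer to non-normality is a rank test. For a positive, right-skewed outcome on which treatment acts proportionally, raw change depends on baseline severity, and ranking raw changes does not remove that dependence. A log scale would.
4. Mann–Whitney compares two groups, so it is not the rank counterpart of a three-arm ANOVA.

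At stake are consistency of the results and, for some outcomes, power in a trial of at most 45 people. Validity of the p-values is not.

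**Working it through.** **The plan's own figures.** 3 × (10 + 5) = 45 reproduces, and losing 5 of 15 leaves 10. The 10 per group is tied to "90% reliability to identify a relevant outcome will be present at the bidirectional α level of 0.05", but no difference or SD is given, so it cannot be reproduced. Solving n = 2(z₀.₉₇₅ + z₀.₉₀)²/d² for n = 10 gives d = √(2 × 10.51/10) = 1.45 (1.53 with the t distribution). For this point only the arm size of 10 to 15 matters.

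**How often the arms get different verdicts.** If each arm fails the normality check with probability p, then P(mixed across three arms) = 1 − p³ − (1 − p)³.

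- Truly normal data, 5% check (p = 0.05): 1 − 0.0001 − 0.8574 = 14%. Simulated: 14–16%.
- p = 0.141 (simulated rate; log-SD 0.5, correlation 0.5, n = 10): 1 − 0.003 − 0.634 = 36%. Simulated: 36%.
- p = 0.316 (log-SD 0.8, correlation 0.5, n = 10): 1 − 0.032 − 0.320 = 65%. Simulated: 67%.
- The maximum is at p = 0.5: 1 − 0.125 − 0.125 = 75%.

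**Power, first set of assumptions.** Lognormal pre and post values with log-SD 0.3–1.0 at each visit and pre/post correlation 0.5–0.7. A multiplicative effect in one arm is sized for about 80% power with log-scale ANCOVA. The check is Shapiro–Wilk at 5% per arm on change; any rejection leads to Kruskal–Wallis (standing in for the rank test that the plan lacks), otherwise ANOVA. There were 1,200–2,000 runs per scenario, a simulation SE of up to about 1.4 points. The effect differs by row, so compare within rows only. Loss = 1 − (rule on raw change)/(ANOVA on log change).

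| n per arm | log-SD | corr. | ANOVA, log change | Rule, raw change | Fixed Kruskal–Wallis, raw change | Loss | Mixed verdict |
|---|---|---|---|---|---|---|---|
| 10 | 0.3 | 0.6 | 69.5% | 58.3% | 57.5% | 16% | 22% |
| 10 | 0.5 | 0.5 | 66.0% | 46.0% | 46.6% | 30% | 36% |
| 10 | 0.5 | 0.7 | 74.7% | 54.9% | 55.3% | 27% | 40% |
| 10 | 0.8 | 0.5 | 67.7% | 37.4% | 38.9% | 45% | 67% |
| 10 | 0.8 | 0.7 | 72.4% | 42.5% | 43.3% | 41% | 69% |
| 10 | 1.0 | 0.6 | 72.1% | 38.9% | 40.1% | 46% | 75% |
| 15 | 0.3 | 0.6 | 67.7% | 60.1% | 58.7% | 11% | 28% |
| 15 | 0.5 | 0.5 | 71.1% | 52.7% | 53.7% | 26% | 50% |
| 15 | 0.5 | 0.7 | 72.3% | 57.4% | 58.0% | 21% | 52% |
| 15 | 0.8 | 0.5 | 67.3% | 42.5% | 43.5% | 37% | 74% |
| 15 | 0.8 | 0.7 | 72.5% | 49.3% | 50.4% | 32% | 74% |
| 15 | 1.0 | 0.6 | 69.9% | 43.5% | 44.1% | 38% | 74% |

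With two-arm runs included, the loss at log-SD 0.5–1.0 spans 21–50%.

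**Power, second set of assumptions.** Between-person log-SD 0.5–0.8, visit-to-visit log-SD 0.3, true ratios 1.0/0.85/0.6.

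- n = 10: 39–44% under the rule on raw change against 62–63% on log change. The loss runs from 1 − 44/62 = 29% to 1 − 39/63 = 38%.
- n = 15: 59–62% against 84–85%. The loss runs from 1 − 62/84 = 26% to 1 − 59/85 = 31%.
- Mixed verdicts when change scores are checked: 52–75%.

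**What causes the loss.** In every row of the table the rule and a fixed Kruskal–Wallis test agree within 1.5 points, which is simulation noise. Under the second set at n = 10, the rule gives 41–43%, fixed Kruskal–Wallis 42–43% and fixed raw-scale ANOVA only 28–37%. The same data-driven rule applied to log change gives 63–64%, as good as a fixed log-scale ANOVA. The raw change scale causes the loss, not the switching.

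**Where the loss shrinks.**

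- Additive shift on a skewed outcome: rule 67.9% against log ANCOVA 74.6% at n = 10 (loss 9%), and 86.0% against 89.0% at n = 15 (loss 3%).
- Normal outcome: 75.3% against 83.6% for ANCOVA at n = 10, and 78.1% against 86.0% at n = 15 (loss 9–10%).

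**Type I error.** Under no effect, the between-arm rule rejects in 3.9–5.3% of trials.

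**The case against.** The strongest reply is that the rule does little harm. Choosing the test from the data costs essentially no power, beats a fixed raw-scale ANOVA for skewed outcomes, and leaves the false-positive rate near 5%. That stands. A reader might infer that picking the test by distribution is what lowers power, or that it produces false positives; the calculations support neither. The type I result does assume one three-group rank test. Unadjusted pairwise Mann–Whitney tests were not simulated.

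Second, a reader might infer a fixed power loss of about a third. The protocol gives no SD, skewness, correlation or form of effect, so no single figure can be attached to this plan. That treatment acts as a ratio is an assumption.

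Third, the raw change scale is read from the absence of any transformation, and scale is often left to an analysis plan. This stands in part. If arms are compared by ranks of the 2-month values, a log transform changes nothing. But the article is not silent on what follows a finding of non-normality: it prescribes rank tests, and that rule can be criticised.

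Fourth, a reader might infer that the between-arm comparison mixes tests. It does not: it uses one test per outcome. Mixing concerns only the within-arm pre/post tests, and only if normality is judged per arm, which the text leaves open.

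Finally, EMG is already normalised to % MVC, so it cannot be treated as a raw amplitude varying several-fold between people. A log of bacterial counts plus one is doubtful if many samples are zero. Both limits are accepted.

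**Conclusion.** The point holds as one of consistency and efficiency. The stated rule selects tests from arms of 10 to 15, ties the normality condition to the variables instead of the within-person differences, answers non-normality with raw-scale ranks, and names a two-group test for three groups.

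- **Consistency:** if normality is judged per arm, within-arm tests for one outcome differ between arms in about 50–75% of trials under the second set of lognormal assumptions. The first set gives 36–74% at log-SD 0.5–0.8, and truly normal data about 15%.
- **Power:** roughly 20–50% of between-arm power is lost on raw change relative to log change, conditional on right skew with log-SD 0.5–1.0 and a proportional effect. The loss is 11–16% at log-SD 0.3. With additive effects it is only 3–9%, and that is against a baseline-adjusted model, so little or none can be put down to scale.
- **Validity:** type I error is not inflated with a three-group rank test.

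The skewness, the correlation and the ratio effect are assumptions throughout. The change is worth making because it is cheap and the sample is small.

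**What to change.** In Statistical analysis, delete the distribution-dependent choice and pre-specify for every outcome one model and one scale, used in all three arms:

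- a linear model of the 2-month value on arm and baseline (ANCOVA);
- log scale for AHI (as log(AHI + 1)), cortisol and salivary flow, reported as geometric-mean ratios with 95% CI;
- raw scale for mouth opening;
- for normalised EMG (% MVC), a scale fixed before data are seen;
- for *P. aeruginosa*, presence/absence or a rank method if zeros are common;
- rank tests only as a labelled sensitivity analysis, with Kruskal–Wallis for the three-arm comparison.

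The cost is analysis wording only, with no added participants, visits or measurements. The downside is that some effects are read as ratios and zeros need a stated offset.

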#### Protocol for polysomnography

All patients will undergo the PSG type II home sleep test (Embla Embletta MPR + PG ST + Proxy; Natus, CA, USA) in their own house. The PSG will be performed prior to and after 2 months of all proposed therapies. During the night, a sleep technician will visit each patient’s home for examination preparation. All recording sensors will be placed according to recommended PSG techniques, using a gel-covered transducer, tapes, or elastic straps. The following biological signals will be recorded simultaneously and continuously: six channels for the electroencephalogram (EEG) (F4–M1, C4–M1, O2–M1, F3–M2, C3–M2, O1–M2), two channels for the electrooculogram (EOG) (E1–M2, E2–M2), four channels for the surface electromyogram (muscles of the submentonian region, anterior tibialis muscle), one channel for the electrocardiogram (derivation V1 modified), two channels for airflow (oronasal thermistor, nasal pressure transducer), two channels for respiratory effort (chest and abdomen, via x-trace belts), one channel for snoring, and one channel for body position, via EMBLA sensors. Arterial oxygen saturation (SaO_2_) and heart rate will be recorded via an EMBLA oximeter. All sleep staging and EEG arousals, respiratory events, and leg movements will be visually scored according to the *American Academy of Sleep Medicine (AASM) Manual for the Scoring of Sleep and Associated Events*, version 2.2, which is the definitive reference for standardized sleep monitoring and scoring [37]. The patients will be instructed to remain as relaxed as possible and to sleep naturally, as if at home. All signals will be recorded continuously. In the morning, an experienced polysomnography technician will remove the PSG equipment from the patient. A sleep physician will read and interpret all PSG examinations.

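### The between-arm test names no baseline adjustment and does not define its response, which gives up precision in arms of 10 to 15

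*Protocol article*

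**What the plan says.** The Statistical analysis section of the protocol article gives two kinds of test.

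- Within person: a paired t "test will be used in order to compare continuous variables with normal distribution, prior to and after polysomnography", with Wilcoxon as the non-normal alternative.
- Between arms: "The groups will be compared to one another using ANOVA", or the Mann–Whitney U test where the distribution calls for it.

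The section on the phases of the sEMG examination keeps the same two comparisons apart: "The obtained data will be compared among each group and among each person with themselves". The article nowhere states the response for the between-arm test, and it mentions no ANCOVA or baseline covariate.

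Baseline values will exist for the main outcomes. The sEMG phases section places sEMG and bite force before therapy and again at 2 months in Groups 1 to 3. For sleep, "The PSG will be performed prior to and after 2 months of all proposed therapies". The Methods part of the Abstract applies the same two time points to the study's methods generally, saliva included.

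On design, "the subjects will be randomly distributed into the three intervention groups" by sealed envelopes, and no stratification is described. The Sample size section plans for arms "with 10 subjects deemed necessary in each group, to which five individuals will be added to compensate for possible dropouts".

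**The concern.** All three arms receive an active therapy. Within-arm before-and-after tests cannot separate a therapy effect from regression to the mean, so the between-arm test carries the randomised evidence. As written, that is the test with no baseline adjustment.

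Two things are at stake. The first is precision: with 10 to 15 per arm, a baseline already collected is the cheapest source of power available. The second is the reading of the single trial that will be run: in arms this small a sizeable baseline difference can easily arise by chance, and an unadjusted comparison then carries part of it into the estimate.

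**Working it through.** **Inputs from the article.** Three arms; 10 per arm required plus 5 for dropout; 45 recruited; two-sided alpha 0.05; 90% power.

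**The plan's own figure.** 3 × (10 + 5) = 45 agrees. The 10 per arm cannot be reproduced, because no numerical effect size or SD is given. Solving backwards, 10 per arm gives 90% power for a standardised difference of 1.53 (two-sample t), or f = 0.69 (three-arm ANOVA). Nothing below depends on this.

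**Assumed.** The correlation r between baseline and 2-month value is not in the article. I take 0 to 0.8.

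**Precision.** Take the variance of an arm difference from 2-month values as 1. Change scores have 2(1 − r) and ANCOVA has 1 − r². Estimating the slope multiplies the ANCOVA figure by 1 + 1/(3n − 5), which is 1 + 1/25 = 1.04 at n = 10 and 1 + 1/40 = 1.025 at n = 15. ANCOVA relative to change is (1 − r²)/[2(1 − r)] = (1 + r)/2.

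| r | 2-month value | Change | ANCOVA | ANCOVA × 1.04 (n = 10) | ANCOVA / change, before factor |
|---|---|---|---|---|---|
| 0 | 1 | 2.00 | 1.00 | 1.04 | 0.50 |
| 0.3 | 1 | 1.40 | 0.91 | 0.95 | 0.65 |
| 0.5 | 1 | 1.00 | 0.75 | 0.78 | 0.75 |
| 0.7 | 1 | 0.60 | 0.51 | 0.53 | 0.85 |
| 0.8 | 1 | 0.40 | 0.36 | 0.37 | 0.90 |

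Break-even at n = 10, on variance alone: against 2-month values, 1.04(1 − r²) = 1 gives r = 0.20; against change, 1.04(1 + r)/2 = 1 gives r = 0.92. Between these values ANCOVA has the smaller variance on either reading of the response.

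**Power.** Simulated global F test, 20,000 replicates, normal data, arm means 0, 0.5 and 1 SD (an illustrative scenario). Entries are ANOVA on 2-month values / ANOVA on change / ANCOVA, in %.

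| r | n = 10 per arm | n = 15 per arm |
|---|---|---|
| 0 | 45 / 25 / 44 | 65 / 36 / 64 |
| 0.3 | 46 / 34 / 48 | 65 / 50 / 69 |
| 0.5 | 46 / 45 / 56 | 65 / 66 / 78 |
| 0.7 | 46 / 68 / 74 | 65 / 87 / 91 |
| 0.8 | 46 / 86 / 88 | 65 / 97 / 98 |

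With no true effect, all three methods rejected in about 5% of replicates.

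**Chance imbalance.** The baseline difference between two arms has SD √(2/n), in units of the outcome SD.

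- n = 10: √0.2 = 0.447; 0.5/0.447 = 1.12; two-sided probability 26%.
- n = 15: √0.133 = 0.365; 0.5/0.365 = 1.37; two-sided probability 17%.
- At least one of the three pairs beyond 0.5 SD (simulated): 50% and 36%.

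**What an imbalance does.** Given a baseline difference of δ SD and equal variances, the expected shift in the arm difference is rδ for 2-month values and −(1 − r)δ for change. With δ = 0.5 and r = 0.5 these are +0.25 and −0.25 SD; with r = 0.7 they are +0.35 and −0.15 SD. ANCOVA removes the shift if the relation is linear.

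**The case against.** *The response may be the change, so the baseline is used.* This stands as far as it goes. A reader might infer that the plan discards the baseline altogether, but the article does not say so: that would be true only if 2-month values are compared. A group-by-time ANOVA is not excluded either; with two time points its interaction test is the change-score ANOVA. If change is meant, the loss is smaller at high correlation: 1/0.85 = 1.18 at r = 0.7 and 1/0.90 = 1.11 at r = 0.8, before the small-sample factor.

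*Randomisation makes the unadjusted test valid.* Correct. A reader might infer a biased or invalid analysis. The documents do not support that: over repeated randomisations the unadjusted difference is unbiased, its standard error allows for chance imbalance, and type I error stays about 5%. The bias is only conditional on the imbalance that happens to occur.

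*A condensed article leaves model terms to a fuller document.* In part. A fuller plan may name a covariate. But the article does name the between-arm test, and the test it names has no baseline term, so the stated choice can be judged. Its silence on stratification does not show that allocation was unrestricted, and the point does not need that.

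*Not every outcome has a baseline.* Correct. Under Quality control, side effects, acceptance and satisfaction are assessed only after treatment, and compliance is recorded only in the oral appliance arm during use. ANCOVA cannot apply to these.

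*The gain rests on an assumed correlation.* Correct. At r = 0.3 the gain over 2-month values is only about 5% after the small-sample factor. The worst-case imputation planned for missing data could also alter r.

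**Conclusion.** The point holds as one of efficiency and protection against chance imbalance. The between-arm response is undefined and no baseline adjustment is named, although the main outcomes have a baseline in every arm.

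At 10 per arm and after the small-sample factor, ANCOVA would cut variance against 2-month values by about 5% at r = 0.3, 22% at r = 0.5, 47% at r = 0.7 and 63% at r = 0.8. Against change scores, before that factor, the cuts are 35%, 25%, 15% and 10%. The worst case examined is r = 0, where about one point of power is lost against 2-month values.

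A reader might take the r = 0.5 figure as a flat gain of one third in patients (1/0.75 = 1.33). That omits the cost of the slope (1/0.78 = 1.28 at 10 per arm) and depends on a correlation that the article does not give. The sizes assume approximate normality, a linear relation and equal variances at the two time points. The change should be made; the trial is not invalid without it.

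**What to change.** In the Statistical analysis section, state that for each continuous outcome with a baseline the between-arm analysis is an ANCOVA of the 2-month value on arm and that outcome's own baseline, reported as adjusted arm differences with 95% CIs. This also settles the undefined response.

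For skewed outcomes, name in advance either a transformation that allows zeros or a rank-based ANCOVA. A plain log fails if a bacterial count or an apnea/hypopnea index is zero, so any added constant should be fixed beforehand. State that outcomes without a baseline (satisfaction, acceptance, side effects, oral appliance compliance) are outside this rule.

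The cost is one degree of freedom per analysis, affordable with 30 to 45 participants, and the wording change. No new data are needed.
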